## Abstract

**Background:**

The current standard for Prostate Cancer (PCa) detection in biopsy-naïve men consists of 10–12 systematic biopsies under ultrasound guidance. This approach leads to underdiagnosis and undergrading of significant PCa while insignificant PCa may be overdiagnosed. The recent developments in MRI and Contrast Enhanced Ultrasound (CEUS) imaging have sparked an increasing interest in PCa imaging with the ultimate goal of replacing these “blind” systematic biopsies with reliable imaging-based targeted biopsies.

**Methods/design:**

In this trial, we evaluate and compare the PCa detection rates of multiparametric (mp)MRI-targeted biopsies, CEUS-targeted biopsies and systematic biopsies under ultrasound guidance in the same patients. After informed consent, 299 biopsy-naïve men will undergo mpMRI scanning and CEUS imaging 1 week prior to the prostate biopsy procedure. During the biopsy procedure, a systematic transrectal 12-core biopsy will be performed by one operator blinded for the imaging results and targeted biopsy procedure. Subsequently a maximum of 4 CEUS-targeted biopsies and/or 4 mpMRI-targeted biopsies of predefined locations determined by an expert CEUS reader using quantification techniques and an expert radiologist, respectively, will be taken by a second operator using an MRI-US fusion device. The primary outcome is the detection rate of PCa (all grades) and clinically significant PCa (defined as Gleason score ≥7) compared between the three biopsy protocols.

**Discussion:**

This trial compares the detection rate of (clinically significant) PCa, between both traditional systematic biopsies and targeted biopsies based on predefined regions of interest identified by two promising imaging technologies. It follows published recommendations on study design for the evaluation of imaging guided prostate biopsy techniques, minimizing bias and allowing data pooling. It is the first trial to combine mpMRI imaging and advanced CEUS imaging with quantification.

**Trial registration:**

The Dutch Central Committee on Research Involving Human Subjects registration number NL52851.018.15, registered on 3 Nov 2015. Clinicaltrials.gov database registration number NCT02831920, retrospectively registered on 5 July 2016.

## Background

The incidence of PCa has increased in the 1990’s, due to increased awareness and prolific Prostate Specific Antigen (PSA) screening. Although in the United States this trend has partly reversed, PCa is still the most common cancer in men representing 21% of cancer cases and it is estimated that 180,890 men will be diagnosed with PCa in United States in 2016 [1]. In Europe the incidence has increased, with 417,00 new PCa diagnoses in 2012 [2]. According to current standards, patients with a clinical suspicion of PCa based on elevated serum PSA and/or digital rectal examination should undergo 10–12 systematic transrectal ultrasound (TRUS)-guided prostate biopsies to confirm the diagnosis [3]. These systematic “blind” prostate biopsies lead to a considerable rate of overdiagnosis of clinically insignificant PCa as well as underdiagnosis and undergrading of significant PCa [4]. Image - guided targeted biopsy approaches have been proposed to address these problems [5]. Prostate cancer imaging has thus far developed on two platforms: MRI and Ultrasound. On the MRI platform, multiparametric MRI(mpMRI) in which diffusion - weighted MRI and dynamic contrast- enhanced MRI sequences are added to anatomical T2-weighted imaging has become the standard for PCa imaging [6]. A 2015 systematic review on the accuracy of mpMRI for the detection of prostate cancer found 12 studies and reported a negative predictive value for the detection of clinically significant prostate cancer between 63 and 98% and positive predictive values of 34–68% [7]. However, these results should be interpreted with caution since several used biopsy pathology as the reference standard to calculate sensitivity and specificity. Several meta-analyses have addressed the value of mpMRI - targeted biopsy cores and these show an improved per-core detection rate and a beneficial increased per-patient detection rate in patients with a persistent clinical suspicion after prior negative biopsies [5, 8]. The 2016 update of the EAU (European Association of Urology) guidelines on PCa now recommends performing mpMRI in these patients. However, at this point, the value of using mpMRI and MRI-targeted biopsies at initial biopsy in biopsy-naïve patient is debated [3]. Even though high negative predictive values for detecting significant prostate cancer have been reported, significant disease can still be missed by MRI - targeted biopsy. Furthermore, considerable heterogeneity and risk of selection bias of published results exists. [8, 9]. The EAU guidelines therefore recommend combining systematic and targeted biopsies [3]. The review by Van Hove et al. shows a 1–43% absolute and 2–430% relative increase in per-patient detection rate can be achieved by adding mpMRI - targeted cores to systematic cores [9]. Several methods of using the information obtained by mpMRI to target the region of interest with prostate biopsies exist: in cognitive targeting, the operator makes a visual estimation of where the MRI lesion is located during a TRUS-guided biopsy procedure. Taking in-bore biopsies during MRI scanning reduces the risk of targeting error but due to its magnet time consuming and therefore costly nature, it is not used often. Fusion devices have been developed that register the MRI images and US together, guiding the observer towards the MRI lesion during the TRUS procedure [10, 11].

Prostate cancer may be visible on standard B-mode TRUS. However, the sensitivity is generally reported to be around 11–35% and the positive predictive value is often cited to be between 17 and 57%, although some studies have shown slightly better numbers [12, 13]. Hence, B-mode ultrasound is widely regarded as insufficiently accurate for tumor detection making systematic ultrasound-guided biopsies necessary. A conclusion that is supported by the guidelines [3, 14]. Contrast - Enhanced Ultrasound (CEUS) has been proposed to improve the accuracy of TRUS to detect Prostate Cancer. In CEUS, an intravascular Ultrasound Contrast Agent (UCA) is used to visualize the changes in vascularity that are typical for significant PCa, particularly angiogenesis. It has been demonstrated that angiogenesis is essential for prostate tumors to progress from small indolent lesions below 2 mm in size to clinically significant disease [15]. The UCA’s consist of gas-filled micro bubbles of 1–10 μm with a lipid or protein shell that have an intravascular lifespan of several minutes. A systematic review on CEUS demonstrated a sensitivity and specificity of 70 and 74% or PCa detection. It must be noted that this meta-analysis contains a mixture of biopsy - controlled studies and prostatectomy - controlled studies as well as different variants of CEUS. Of particular interest is the analysis by van Hove et al. that shows a 2–8% absolute or 7–35% relative increase in per-patient detection rate was attained by adding CEUS - targeted cores to systematic biopsy protocols [9]. This analysis indicates improved per-patient detection rates can be achieved with adding CEUS-targeted cores, however CEUS-targeted biopsy at this point cannot replace systematic biopsy. Traditional drawbacks of CEUS are its user-dependency, the limited number of planes that can be visualized in one setting, and the fact that the cues that signify a suspicious focus are subtle and present in the image studies in a matter of seconds. To overcome these drawbacks, computer-aided quantification, a relatively new method to analyze CEUS recordings, is used to assist in the CEUS interpretation [16]. In the present trial, we will use the Contrast Ultrasound Dispersion Imaging (CUDI) method with computer-aided quantification developed at the Eindhoven University of Technology [17]. In short, this method entails constructing per-pixel Time-Intensity-Curves (TICs) during the UCA inflow phase of CEUS recordings. Several parameters calculated from the spatiotemporal distribution of these TICs have shown very promising results in predicting PCa presence with Area Under the Curve (AUC) values reaching up to 0.88–0.89 [17, 18]. These results were obtained by estimating how well CUDI could predict whether pixels belonged to a benign or malignant region of interest using radical prostatectomy specimens as the reference standard. In the present study we will evaluate the value of targeted biopsy procedures with mpMRI and CEUS + CUDI quantitative imaging by performing both procedures with systematic biopsies in the same patients scheduled for initial prostate biopsies. This way we will be able to determine how successful these tools can be used for targeting biopsies and how these targeting procedures compare to each other and to systematic biopsies. Additionally, we will analyze to what extent the imaging tools overlap in the tumors they detect or miss, and therefore to what extent they can be used complementary to each other.

## Methods/design

### Study objectives

#### Primary

To compare the per-patient (significant) prostate cancer detection rate for mpMRI-US fusion - targeted biopsies and CEUS + CUDI-targeted biopsies with 12-core systematic biopsies.

#### Secondary

To evaluate the value of using both mpMRI and CEUS + CUDI for targeted prostate biopsies.

### Expected outcomes

Based on previous studies that used a fusion device to take 2–4 mpMRI - targeted biopsy cores in biopsy naïve patients, we expect a per-patient cancer detection rate (CDR) between 40–54% for the mpMRI - targeted biopsies. With the targeted cores, CDRs were achieved that were between 1% absolute higher and 13% absolute lower than the CDRs of systematic biopsies in the same series. Of note is that the biggest series used 3 different methods of targeting the mpMRI cores: cognitive targeting, rigid fusion and elastic fusion. Their best result with targeted cores relative to the systematic cores was achieved with the elastic fusion method (33% CDR for systematic cores and 47% for targeted cores). The Artemis (Eigen, Grass Valley, USA) fusion system that will be used in our trials uses elastic registration. The majority of series have performed a similar analysis in patients with previous negative systematic biopsies or mixed patient cohorts which tend to show a better performance of targeted cores relative to systematic cores [19]. In our biopsy naïve cohort we expect to find a per-patient CDR for all PCa grades that is in the same range as the systematic biopsies. In contrast, we expect the per-patient CDR for clinically significant (Gleason >3 + 4) disease of the mpMRI - targeted biopsies to be relatively higher compared to systematic biopsies.

Limited data is available for the value of CEUS-targeted cores. Van Hove et al. reviewed 6 studies that compared the CDRs for CEUS-targeted biopsies and systematic biopsies [9]. They report that targeted biopsy cores achieved CDRs between 13% absolute lower and 4% absolute higher than systematic cores in these heterogeneous studies with mixed patient groups and various CEUS variants used. None of the studies in this review have included the use of quantitative techniques. A previous study done in our own institution, that retrospectively correlated CEUS imaging with and without quantification with systematic biopsy results, showed improved significant PCa detection with the use of quantification. In 82 patients, 5.6% of biopsy locations that were classified benign on imaging showed clinically significant disease when quantification software was used, compared to 8.5% for CEUS without quantification [20]. Unfortunately, no targeted biopsies were taken in this retrospective analysis. We hypothesize that the use of CUDI quantification software in our current study will result in a CDR for significant disease up to the level of systematic biopsies or better. To our knowledge, there are no published data on the complementarity of mpMRI and CEUS in prostate cancer detection and biopsy targeting. Based on the available data on the separate techniques, we expect that the combination will result in a CDR higher than that of systematic biopsies, especially for the detection of clinically significant disease.

### Study design

This study is a prospective in-vivo study in humans in which we perform MRI imaging and CEUS imaging in biopsy-naïve patients scheduled for prostate biopsies. Targeted prostate biopsies based on these images will be taken besides current standard of care systematic biopsies. Since both imaging modalities and targeted biopsies will be performed in the same patients, every patient effectively serves as his own control. Patients will undergo mpMRI imaging and CEUS imaging approximately 1 week before the scheduled biopsy appointment. During this week, MRI reading will be performed by a specialized uroradiologist with approximately 10 years of prostate mpMRI experience using the European Society of Urogenital Radiology (ESUR) Prostate Imaging Reporting and Data System standardised scoring system, version 2 (PIRADS v2) [21]. The radiologist is blinded to CEUS and CUDI results. The CEUS recordings will be analysed using the CUDI quantification technique. An observer experienced in CEUS of the prostate will read the CEUS recordings and CUDI-maps, while blinded to the MRI results. Before the biopsy procedure, the MRI - based biopsy targets and CEUS + CUDI - based biopsy targets are therefore predetermined independently from each other. During the biopsy session, approximately 1 week after the imaging is recorded, a physician who is blinded to all imaging results and the targeted biopsy procedure will first perform the standard 12-core systematic biopsy to prevent potential bias by post-biopsy haemorrhage seen on ultrasound after targeted biopsies. Then a separate observer, using an MRI-US fusion device, takes a maximum of 4 targeted biopsies from the MRI lesions delineated by the radiologist followed by a maximum of 4 targeted cores from the CEUS + CUDI lesions identified by the CEUS expert. Per-patient CDRs and tumor differentiation grades are compared between each of the biopsy regimens: MRI - targeted biopsies, CEUS + CUDI - targeted biopsies and systematic biopsies.

### Population

Two hundred ninety-nine biopsy-naïve men above the age of 18 years that are scheduled for initial prostate biopsies on the basis of a suspicious DRE and/or elevated serum PSA (above 3 ng/ml) will be included in the study. Patients will be recruited at the AMC University Hospital and all study procedures will be performed at that institution. Exclusion criteria are mostly related to the MRI, the UCA used for CEUS imaging and biopsy procedures(Table 1). Patients will be informed about study procedures, risks and benefits, and are only included after written informed consent has been obtained.

**Table 1 Tab1:** Inclusion and exclusion criteria

Inclusion Criteria	Exclusion Criteria
1. Age ≥ 18 years 2. Signed informed consent 3. Referred for prostate mpMRI and prostate biopsies	1. Is incapable of understanding the language in which the information for the patient is given 2. Has undergone previous prostate biopsies 3. Active (urinary tract) infection or prostatitis 4. History of any clinically evidence of cardiac right-to-left shunts 5. Receives treatment that includes dobutamine 6. Severe pulmonary hypertension (pulmonary artery pressure >90 mmHg) or uncontrolled systemic hypertension or respiratory distress syndrome 7. Any medical condition or other circumstances which would significantly decrease the chances of obtaining reliable data, achieving study objectives, or completing the study 8. Any (further) contraindication to undergo mpMRI or CEUS imaging

*mpMRI* multiparamteric Magentic Resonance Imaging, *CEUS* Contrast - Enhanced Ultrasound

### Study procedures

#### Multiparametric magnetic resonance imaging

Prior to the mpMRI acquisition, a rectal preparation with a laxative suppository (Bisacodyl) will be performed and just before mpMRI scanning an anti-Peristaltic Drug (Buscopan or Glucagon) will be given. mpMRI will be performed in supine position on a 1.5 Tesla AVANTO® MRI scanner (Siemens Healthcare, Erlangen, Germany) or on a 3 Tesla INGENIA® without endorectal coil (Philips Medical Systems, Best, The Netherlands). The scanning protocol starts with T2-weighted sequences which will be performed in sagittal, coronal and axial planes covering the prostate and seminal vesicles. Then, a single-shot-echo planar diffusion-weighted sequence with fat suppression pulse is acquired and ADC maps are calculated. Finally, dynamic contrast-enhanced images using 0.1 mmol of gadopentetate dimeglumine (Gadolinium DTPA, Gadovist) per kg of body weight, are obtained. More details on the mpMRI conduct can be found in Table 2. mpMRI will be evaluated by a specialized uroradiologist (blinded for CEUS results) on prostate volume and area’s suspicious for PCa. Scoring of suspicion will be performed using PIRADS v2 [21]. All lesions will be marked and delineated for MRI-TRUS fusion using the ProFuse (Eigen, Grass Valley, USA) software package that accompanies the Artemis fusion device.

**Table 2 Tab2:** MRI conduct

mpMRI Conduct		
Unit	Philips 3 Tesla INGENIA®	Siemens 1.5 Tesla AVANTO®
Slice Thickness		
T2-Weighted	3 mm	3 mm
DW-MRI	4 mm	5 mm
DCE-MRI	2 mm	4 mm
T2-weighted planes	axial, coronal and sagittal	axial, coronal and sagittal
DCE-MRI		
Temporal resolution	5.00 s	3.06 s
Post-processing model	Tofts model using Dynacad (In Vivo, Best, The Netherlands)	Tofts model using Dynacad (In Vivo, Best, The Netherlands)
DW-MRI,		
B-values,	B0, B100, B1000	B50, B800
Imaging sets	ADC, calculated B1500	ADC
Quantitative analysis	primarily qualitative, quantitative in unclear cases	primarily qualitative, quantitative in unclear cases

*mpMRI* multiparamteric Magentic Resonance Imaging, *DW-MRI* Diffusion - Weighted Magnetic Resonance Imaging, *DCE-MRI* Dynamic Contrast- Enhanced Magnetic Resonance Imaging

#### Contrast-enhanced ultrasound and quantification

Contrast Ultrasound scanning will be performed in the left-lateral decubitus position using a Philips IU22 ultrasound scanner with a C10–3V endocavity probe (Philips Healthcare, Bothell, USA) with power modulation at 3.5 MHz and a mechanical index (MI) of 0.06. A total of four CEUS recordings will be made: from the base, mid-base, mid apical and apical planes. The locations of these planes within the prostate are stored using the Artemis fusion device, for future targeting of suspicious lesions. Each of the 2 min recordings will be started following the administration of a 2.4 mL bolus of the contrast agent SonoVue® (Bracco, Geneva, Switzerland) through an intravenous cannula. After each recording a pause of 3 min is observed to allow sufficient UCA breakdown to assess the inflow of the next UCA bolus. The CEUS recordings are anonymized and transferred through a secure connection to the Eindhoven University of Technology for CUDI quantitative analysis. The CUDI maps are transferred back to the physicians to aid in the CEUS interpretation and selection of the biopsy targets. This is done by a CEUS expert, who is blinded to MRI results.

#### Biopsy procedure

Patients are prepared for the biopsy procedure with a 2 day course of fluoroquinolone prophylaxis. The biopsy procedure is performed in the left-lateral decubitus position using the same ultrasound device and probe as used for the CEUS imaging. A first operator blinded to the targeted biopsy procedure planning and imaging results will take a standard 12-core systematic biopsy that includes 2 medial and 4 laterally directed cores of the peripheral zone of the prostate on each side. Then a second physician, using the Artemis fusion device for guidance, takes a maximum of 4 biopsies from targets designated by the radiologist and a maximum of 4 biopsies from the targets designated by the CEUS expert. The needle biopsy cores will be analysed for tumour presence and grading by our institution’s specialized uropathologist in accordance with current pathology guidelines.

### Sample size and statistical analysis

#### Statistical analysis

The per-patient PCa detection rates of both targeted biopsy regimens will be tested separately for non-inferiority against current standard 12-core systematic biopsies using a one sided non-inferiority test for correlated proportions [22, 23]. To evaluate if image- targeted biopsies can be used complementarily, we will also perform the same comparative analysis for the targeted biopsy results combined, compared to the systematic biopsies. Moreover, the per-patient CDR’s of all three biopsy protocols will be directly compared using McNemars test for correlated proportions. The same analyses will be performed including all tumors and including clinically significant tumors only, defined as PCa with a Gleason score ≥3 + 4 = 7.

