#### Sample size calculation

The sample size calculation is based on the non-inferiority test between the targeted biopsy procedures and the systematic biopsies. For this test we performed a power analysis, with the detection rate for systematic biopsies set at 45% [24], a power of 80% and the significance level (alpha) of 5%. The maximum allowable difference in detection rate for the targeted biopsies to be considered non-inferior to systematic biopsies was set at 1%. We expect a maximum proportion of discordant pairs of 15% and a detection rate difference of 5%. The required sample size according to these specifications is 260 patients. Based on the estimation that 15% of the patients that are scheduled for biopsies will not receive targeted biopsies due to the absence of PCa suspected lesions on imaging; a total number of 299 patients will be enrolled in the study.

Literature shows that of all positive biopsies about 25% is Gleason >6 [25–27]. Results from our institution differ from literature as only 40% of all the patients with PCa at biopsy have a Gleason score 6 PCa, while 60% of them have a Gleason score >6 PCa. Thus, numbers of positive biopsies and Gleason score > 6 are higher than reported in literature. Based on our historical data we expect that by including 299 patients in the study we will find ~65 cases with a Gleason score = 6 and ~100 cases with a Gleason score > 6. For differentiation between Gleason score we hypothesize that we need at least 40 people in both Gleason grade groups.

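### The combined-versus-systematic non-inferiority test, which the plan names as its complementarity evaluation, cannot by itself show that MRI and CEUS complement each other

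*Protocol article*

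**What the plan says.** The secondary objective is broad: "To evaluate the value of using both mpMRI and CEUS + CUDI for targeted prostate biopsies". It names no comparator and no endpoint.

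The Background announces an analysis aimed directly at complementarity: "we will analyze to what extent the imaging tools overlap in the tumors they detect or miss". The same sentence goes on to tie that overlap to how far the tools can complement each other.

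The Statistical analysis section gives the question to a different analysis. Each targeted regimen is first compared separately with systematic biopsy by a "one sided non-inferiority test for correlated proportions". The section then turns to complementarity: "To evaluate if image- targeted biopsies can be used complementarily, we will also perform the same comparative analysis for the targeted biopsy results combined". The only comparator is systematic biopsy, since the analysis is to be done "for the targeted biopsy results combined, compared to the systematic biopsies". The section adds that "the per-patient CDR’s of all three biopsy protocols will be directly compared using McNemars test for correlated proportions". All analyses are run for all tumours and again for Gleason 7 or higher. The combination is not compared with MRI alone or with CEUS alone, and the overlap analysis from the Background is not mentioned.

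For the combination, the Expected outcomes section states a hypothesis against systematic biopsy: "we expect that the combination will result in a CDR higher than that of systematic biopsies".

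**The concern.** Two techniques complement each other to the extent that each finds cancers the other misses. The Background uses the word in this sense. The test named in the Statistical analysis section measures something else, namely how the union of the two techniques compares with systematic biopsy. That comparison mixes the overlap between MRI and CEUS with how well each does against systematic biopsy, and a pass can come entirely from one of them.

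The McNemar test of MRI against CEUS does not fill the gap. It asks whether the MRI-only and CEUS-only cells are equal, not how large they are. Equal detection rates are compatible with complete overlap and with none.

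What is at stake is how the secondary result is read. As worded, a pass produced wholly by MRI could be presented as evidence that the two techniques are complementary, and a failure could hide a real contribution from CEUS. The Discussion lists assessment of complementarity among the things the trial will provide, and it calls CEUS experimental.

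**Working it through.** **Inputs from Sample size calculation:** systematic detection rate 45%, margin 1%, expected difference d = 5 points (read as favouring targeted biopsy), discordant proportion 15%, alpha 5% (one-sided, from Statistical analysis), power 80%, required n = 260, enrolled n = 299.

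**Reproducing the plan's sample size.** For paired proportions, n = (z₀.₉₅ + z₀.₈₀)² × (discordant − d²) / (d + margin)².
- (1.645 + 0.842)² × (0.15 − 0.0025) / 0.06² = 253.3, so 254.
- Two common variants of the variance give 257 and 258. All are within 3% of the stated 260, so the inputs are read correctly.
- A one-sided 2.5% level would give 322 to 328 and does not match.

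**Why the union cannot fall below MRI.** Combined-positive means MRI-positive or CEUS-positive. Adding CEUS can only move a man from systematic-only to concordant positive, or from concordant negative to targeted-only. Enumerating every possible result of the score-type test (1% margin, one-sided 5%) at n = 260 and n = 299 showed no such move that turns a pass into a fail. A pass for MRI therefore guarantees a pass for the combination.

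**Pass probability when CEUS adds nothing.** The combined test is then the MRI test:
Φ[(d + margin) × √n / √(discordant − d²) − 1.645]
- n = 260: Φ[0.06 × 16.12 / 0.384 − 1.645] = Φ(0.874) = 80.9%
- n = 299: Φ[0.06 × 17.29 / 0.384 − 1.645] = Φ(1.057) = 85.5%

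Simulating the score test (200,000 runs) gives 81.4% and 85.9%.

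**Other scenarios.** The CEUS increments and the MRI deficits below are assumptions.

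| MRI minus systematic | Added by CEUS | Combined minus systematic | Combined test passes (n = 260 / 299) |
|---|---|---|---|
| +5 points | 0 | +5 points | 81% / 86% |
| +5 points | 3 points | +8 points | 98% / 99% |
| −6 points | 5 points | −1 point | 5% / 5% |
| −10 points | 8 points | −2 points | 2% / 2% |

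A pass is not sufficient to show that CEUS adds to MRI (row 1), and it is not necessary either (rows 3 and 4).

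**When the test does respond to overlap.** Assume each technique sits exactly at the margin (7% targeted-only, 8% systematic-only), with n = 260. At overlap f within those discordant cells, combined targeted-only is 7% × (2 − f) and combined systematic-only is 8% × f.
- f = 80%: 8.4% against 6.4%, difference +2.0 points, passes 35% of the time.
- f = 50%: 10.5% against 4.0%, difference +6.5 points, passes 95%.
- MRI and CEUS independent given the systematic result: 0.55 × [1 − (1 − 0.07/0.55)²] = 13.1% against 0.45 × (0.08/0.45)² = 1.4%, difference +11.7 points, passes more than 99%.

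**Precision of a direct estimate.** The exact 95% interval for an illustrative 9 of 299 (3.0%) is 1.4% to 5.6%. For 0 of 299 the upper limit is 1.2%.

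**The case against.** The strongest case for the plan has four parts.

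1. **The objective is broader than the increment of one technique over the other.** The hypothesis for the combination is itself stated against systematic biopsy, so the combined test answers a pre-stated question. This stands, and it is the reason to keep the test.

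2. **The overlap analysis is already announced in the Background, and a condensed article may leave its details to a fuller document.** The first half stands. The second does not dispose of the point: the Statistical analysis section does not merely omit detail, it assigns the complementarity question to a named test that measures something else.

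3. **The planned analyses already contain the needed quantities.** On a common denominator, the combined rate minus the MRI rate is exactly the CEUS-only proportion, and those cells feed the McNemar test. This is true of the data. But the plan does not say that this difference will be formed, given an interval, or used to judge complementarity.

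4. **The test is not blind to overlap.** With both techniques at the margin, its pass probability moves from 35% to over 99% as overlap falls. A combination that passes when neither technique passes alone would be informative. This also stands.

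A reader might therefore infer too much: that the plan cannot meet its secondary objective at all, or that a combined pass carries no information. Parts 1 and 4 rule out both readings. Nor does the document say that a pass would be reported as added value of CEUS over MRI; that is a risk created by the wording.

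**Conclusion.** The point holds in a limited form. The combined-versus-systematic test cannot by itself show complementarity, because under the planning values it passes about 81% (n = 260) to 86% (n = 299) of the time when CEUS contributes no additional cancer. It remains a valid test of whether the two techniques together can replace systematic biopsy.

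The 81% and 86% rest on the plan's own values: a 5-point difference favouring targeted biopsy, 15% discordance (which the plan gives as a maximum), a 1% margin and one-sided 5%. A score-type paired test is assumed; a Wald test gives nearly the same result (81.4% and 86.4%). If MRI were only equal to systematic biopsy, the pass probability with no CEUS contribution would be 11% to 12%, so the size depends on how well MRI performs. The logic that a pass for MRI forces a pass for the combination does not. The primary comparisons, the sample size and the conduct of the trial are unaffected.

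**What to change.** In Statistical analysis, make the overlap analysis from the Background the complementarity analysis and define it on one denominator, all biopsied men:

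- the proportion with cancer detected by CEUS-targeted but not MRI-targeted cores;
- the proportion with cancer detected by MRI-targeted but not CEUS-targeted cores.

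Give each an exact 95% confidence interval, for all cancers and for Gleason 7 or higher, and report the full 2×2×2 table of MRI, CEUS and systematic results. On this denominator, a man without targeted cores from a technique counts as not detected by it.

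Keep the combined-versus-systematic test, relabelled as the question whether both techniques together can stand in for systematic biopsy. A superiority test of the combination against MRI alone would add little, because the union cannot be lower; the size of the increment is what matters.

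The cost is a change of wording and a little more analysis of data already collected.
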